### 3.0. THEORETICAL FRAMEWORK

Our frailty rehabilitation program is based on the international consensus guidelines that recommend a **multi-modal approach** to reduce frailty [9] and the **WHO** Public-Health Framework for Healthy Ageing [18] to align community-based health services to meet the complex needs of older adults who are frail. Their call to action is “affordable access to integrated health services that are centered on the needs of older people” [19]. This framework for action is built around the concept of building **intrinsic capacity** (defined as all the physical and mental capacities that an individual can draw on at any point in time) by **promoting capacity-enhancing behaviours** within a supportive environment to **enable functional ability** (defined as health-related attributes that enable people to be and to do what they have reason to value) [19]. Frailty and intrinsic capacity are closely linked constructs given that frailty is the age-related decline of physiological systems, which can profoundly reduce intrinsic capacity [20].

### 4.0. METHODS

**4.1. Design:** In this multi-arm RCT, 324 community-dwelling older adults (aged 65+) with frailty and at high risk for mobility disability will be randomized into one of three arms (**control, exercise only, multi-modal rehabilitation**) stratified by sex, age, and location preference. Rolling recruitment will occur with ten cohorts total (2-3 cohorts per site, n=33 participants per cohort), enrolled across the partner YMCA sites. Blinded assessors will assess clinical outcomes at 0 and 4-months, with an additional 6-months of healthcare utilization via telephone follow-up. The multi-modal intervention is adapted from protocols used in our prior pilot studies and designed to ensure safe training components for frail adults with an emphasis on improving functional ability.

**4.2. Recruitment Process:** Our team (Geras, McMaster University, and Hamilton Health Sciences staff, students/trainees, and volunteers) will collaborate with clinicians (e.g., physicians, nurses, physiotherapists, occupational therapists, case managers) and administrative staff/ services (e.g. HHS Hub) at Hamilton Health Sciences (HHS) (e.g. St. Peter’s Hospital, Juravinski Hospital, Hamilton General Hospital), McMaster University, and St. Joseph’s Healthcare Hamilton (SJHH) to identify potential participants from a variety of units. Additional sources of referral will be from any healthcare provider, including but not limited to, physicians, nurses, physiotherapists, occupational therapists, case managers, within Southern Ontario (external to HHS, McMaster, and SJHH). If requested/approved, these networks will also be provided with brochures, posters, and other study advertisements for recruitment.

A pre-screening referral form will be completed and sent to the research team to determine eligibility. If the referee is external to HHS/McMaster, the referee will be asked to sign a data transfer agreement prior to using

## FRAILTY REHABILITATION: A COMMUNITY-BASED INTERVENTION TO PROMOTE HEALTHY AGING

the pre-screening referral form for sending patient information. Interested individuals in the community may also self-refer by calling or emailing the GERAS Research staff (phone number will be provided on advertising materials) or completing the contact form on the Geras Centre website (mandatory fields include first name, email address or telephone number, and location preference). Telephone pre-screening by the GERAS study staff will assist in identifying individuals prior to a virtual (via telephone) eligibility assessment. During the telephone pre-screening, we will also be asking the participant whether they would prefer a study information package to be mailed to an address of their choice or e-mailed. The study information package includes the following: a one-pager study info sheet and the participant information letter to allow the participant to learn more about the study at their own pace prior to informed consent. Similar studies in primary care with frail elderly report randomization rates of 1 enrolled patient per 6 screened. Our recruitment strategy will include:

- **Acute Care:** Our team will collaborate with clinicians (physicians, nurses, physiotherapists, occupational therapists) in acute care (e.g., at the Juravinski Hospital) to identify potential participants being discharged from medical units under the direction of the unit's director. These individuals will help the team identify and recruit potential participants from acute care by: a) having a member of the research team located at the clinic to directly assist with recruitment (e.g., talking to prospective participants), b) having the clinician discuss and/or distribute advertisement material/study information (e.g., via brochures or smartphrases used in EPIC for patient discharge or visit forms/sheets), or c) asking the clinician to use the Clinical Pre-Screening Referral Form (**Appendix A**; this includes obtaining patient consent for a member of the study team to contact them to arrange a formal study-screening visit via telephone) and send this form to the GERAS research team.
- **Primary Care:** Our team is well connected within primary care (including family medicine leaders Drs. [name] and [name] and family doctor collaborator [name]) and several co-Investigators are part of the [healthtapestry.ca](http://healthtapestry.ca) primary care initiative (Co-led by [name]). Drawing on these networks, we will work with family health teams and general practitioners (GP). For practices with electronic medical records, screening for eligibility is a strategy that has been successfully applied with similarly vulnerable cohorts [21]. Our research team will support family health teams and administer telephone pre-screening. Clinicians may also refer patients directly by completing the Clinical Pre-Screening Referral Form (**Appendix A**) and send to the GERAS research team. **In our region, in a typical family health team (e.g. 4 physicians), there are approximately 6000 patients, with 10% over age 70 (n=600)** (personal communication/query). Recruitment at the clinic may look like: a) having a member of the research team located at the clinic to directly assist with recruitment (e.g., talking to prospective participants), b) having the clinician discuss and/or distribute advertisement material, c) asking to clinician to use the Clinical Pre-Screening Referral Form (Appendix A; this includes obtaining patient consent for a member of the study team to contact them to arrange a formal study-screening visit) and send this form to the GERAS research team, d) having a member of the research team contact patients who have already agreed to be contacted for research studies (e.g., in a research registry at a healthcare organization), and/or e) asking the clinic to perform a database search for potentially eligible participants and subsequently asking the clinic/clinicians to contact/discuss potential study enrollment with these patients (via mail,

## FRAILITY REHABILITATION: A COMMUNITY-BASED INTERVENTION TO PROMOTE HEALTHY AGING

in-person, phone etc.). If option E (database search), with the permission of the clinic, the Geras research team may assist the clinic with mailing.

- **Community:** We already have and continue to establish partnerships with other studies (e.g. GERAS DANCE, community centres and organizations (e.g. Alzheimer’s Society, Osteoporosis Canada). Within the community, research personnel will utilize user-friendly brochures and attend events to promote the study (e.g., at food drives, community centres, libraries, places of religious worship). Research personnel will also connect with local media outlets to advertise for recruitment (i.e., newspapers, television, radio, etc.). In addition, this study will be advertised on the Voice platform (a web-based self-referral through advertising recruitment pathway). The Voice is a community engagement platform that the McMaster Institute for Research on Aging (MIRA) is licensing from the University of Newcastle. Please see Appendix C for more details on recruitment for this study through the Voice.
- **Home Care:** Older adults receiving homecare represent over 50% of emergency room visits at Hamilton Health Sciences (LHIN Personal Communication). Our team is already embedded with the LHIN and will work with LHIN care coordinators who may identify high-risk clients who are frail yet mobile to attend community classes and benefit from this study.
- **External Specialists within Community:** These individuals will help the team identify and recruit potential participants from their clinics. This may be done by: a) having a member of the research team located at the clinic to directly assist with recruitment (e.g., talking to prospective participants), b) having the clinician discuss and/or distribute advertisement material, c) asking the clinician to use the Clinical Pre-Screening Referral Form (**Appendix A**; this includes obtaining patient consent for a member of the study team to contact them to arrange a formal study-screening visit) and send this form to the GERAS research team, d) having a member of the research team contact patients who have already agreed to be contacted for research studies (e.g., in a research registry at a healthcare organization), and/or e) asking the clinic to perform a database search for potentially eligible participants and subsequently asking the clinic/clinicians to contact/discuss potential study enrollment with these patients (via mail, in-person, phone etc.). If option E (database search), with the permission of the clinic, the Geras research team may assist the clinic with mailing.

**4.3. Intake Appointment:** All participants will attend an intake appointment where **eligibility screening**, and **informed consent** will be reviewed by the GERAS study staff. Using the recruitment strategy indicated above in our pilot studies, we recruited 3-4 participants/week with frailty and cognitive impairment (GERAS DANCE) and 3-4 participants/month scheduled for hip or knee replacement surgery (Fit Joints). The loss to follow-up was 20% (GERAS DANCE) and 10% (Fit Joints). Within the literature, the Singapore FIT trial [16], which included also pre-frail individuals, had a low drop-out rate of 4-10% (depending on group assignment).

### 4.4. Eligibility Criteria

#### **Inclusion Criteria:**

- Community-dwelling (not LTC) ≥65 years of age;
- Able to ambulate 25 metres with or without a walking aid;

**FRAILTY REHABILITATION: A COMMUNITY-BASED INTERVENTION TO PROMOTE HEALTHY AGING**

- At high risk for mobility disability/functional limitations as assessed by the John Morley FRail scale (score of  $\geq 2$ );
- Medical clearance from referring clinician, or for self-referrals, medical clearance from family physician to safely participate in exercise and take oral nutritional supplements;
- Can arrange transportation to the YMCA up to 2 times per week;

**Exclusion Criteria:**

- Unable to speak or understand English;
- Currently attending a group exercise program;
- Currently in a drug optimization study/program;
- Currently taking oral nutritional supplements daily;
- Significant cognitive impairment where they may have difficulty following two step commands in group exercise [22];
- Receiving palliative/end of life care;
- Terminally ill;
- Unstable angina or unstable heart failure;
- Another household member enrolled in the study;
- Unable to attend for more than 20% of trial duration.

Participants are eligible to participate as long as they abide by the current COVID-19 protocols at all study sites at the time of enrollment. During the baseline assessment, all eligible participants will have sarcopenia status assessed, by examining physical performance (through the SPPB), prior to randomization. Scores greater than or equal to 12 seconds for the 5-time chair stand test are predictive of sarcopenia. Participants with sarcopenia will undergo additional outcomes to measure changes in muscle mass and strength (see Table 2 for outcomes). Up to 75 participants with sarcopenia will undergo these additional outcomes at baseline and 4-month time points. Participants who complete the 5-time chair stand test in less than 12 seconds are still eligible to participate, provided they meet the other eligibility criteria (listed above) during screening.

**4.5. Randomization:** Stratified block randomization (1:1 randomization ratio) with the allocation sequence generated by a computer will be used to randomly allocate participants to their group assignment. Participants will be stratified based on their sex, age (<80 or  $\geq 80$  years), and location preference. Research staff will obtain informed consent and confirm eligibility and will randomize the participant using Research Electronic Data Capture (REDCap) randomization system, a secure web application for building and managing online surveys and databases. To protect against selection bias, the randomization sequence will be adequately concealed so that investigators/participants are not aware of the upcoming assignment. To protect against ascertainment bias, baseline measures will be assessed **prior** to randomization. Outcome assessors, the study biostatistician, the investigative team, and the steering committee will be blinded to intervention assignments. Research assistants, study intervention personnel (pharmacist, instructors) and participants will not be blinded.

**4.6. Interventions:** Participants will be randomized to one of three arms (control, group exercise only, multi-modal), with the intervention lasting 4-months (**Figure 1**). Each cohort will have at maximum, 11 people

## FRAILTY REHABILITATION: A COMMUNITY-BASED INTERVENTION TO PROMOTE HEALTHY AGING

randomized into each arm for a total of 33 individuals per cohort. **Table 1** summarizes preliminary findings of our network meta-analysis [23]. All participants will receive equal amounts of contact and follow-up by research personnel (e.g., monthly phone-calls, outcome assessments). Participants from all 3 arms will be randomly selected to wear a study ActiGraph accelerometer for the duration of the study, should they consent. The device will collect health information such as raw acceleration data, physical activity intensity, total sleep time, activity bouts, sedentary bouts, sleep efficiency, and energy expenditure, in real time.

**Study Orientation:** During the first session, participants in the multi-modal and exercise only groups will receive an intervention-specific study manual and instructors will provide an orientation for participants so that they know what to expect from their sessions.

**Table 1: Frailty Management – Summary of Evidence for Individual Components**

|                   |                                                                                                                                                                                                                                                                                                                                                                                                                                                                                                                                                                                                                                                                                                                                                               |
|-------------------|---------------------------------------------------------------------------------------------------------------------------------------------------------------------------------------------------------------------------------------------------------------------------------------------------------------------------------------------------------------------------------------------------------------------------------------------------------------------------------------------------------------------------------------------------------------------------------------------------------------------------------------------------------------------------------------------------------------------------------------------------------------|
| SOCIAL     | Rationale: Social interaction associated with better mental and physical health [24], and evidence suggests that group versus individual engagement may offer unique cognitive benefits for older adults [25] as well as peer reinforcement and encouragement.                                                                                                                                                                                                                                                                                                                                                                                                                                                                                         |
| VITAMIN D3 | Dose/Frequency: 1000 IU Vitamin D3 daily [26]
Rationale: Lower levels of Vitamin D levels are consistently associated with lower muscle mass and physical function (including handgrip strength test and SPPB) [27–29]. Meta-analysis [30] demonstrates a positive effect of daily vitamin D supplementation on muscle strength and balance in older adults, an effect influenced by baseline vitamin D deficiency [31,32].                                                                                                                                                                                                                                                                                                                  |
| EXERCISE   | Dose/Frequency: A recent meta-analysis suggests 180 min/week of exercise (with a high challenge to balance) is most effective for fall prevention [14]
Rationale: Combined strength and endurance training (i.e., concurrent training) performed at a moderate weekly frequency (i.e., two times per week) may promote marked gains on muscle hypertrophy, strength and power gains in older adults living with frailty [33]. Balance training is a key component of successful exercise programs for vulnerable older adults [34].                                                                                                                                                                                            |
| PROTEIN    | Dose/Frequency: As piloted in our Virtual Frailty Rehab study, the oral nutritional supplement (ONS) (each serving) contains 225kcal, and 11-12 grams protein (Glucerna, Ensure). Participants are advised to take this with a meal or within 3 hours of exercise on activity days. Participants will be provided with two ONS each day of the study.
Rationale: Adequate protein impacts muscle protein synthesis [35] strength [36,37], and physical function [38,39] in frail or sarcopenic older adults that is enhanced with exercise [39]. Older adults with malnutrition or who are at risk of malnutrition are recommended to consume oral nutritional supplements per day containing at least 400kcal and 30 grams of protein [40]. |
| MEDICATION | Approach: In meta-analyses, improving the appropriate use of polypharmacy in older people can be obtained with use of Beers' criteria and Screening Tool of Older Person's Prescriptions (STOPP)/ Screening Tool to Alert to Right Treatment (START) have demonstrated a reduction in inappropriate prescribing [41].
Rationale: Deprescribing appears to be feasible and generally safe. Patient-specific interventions to reduce polypharmacy may improve longevity and reduce adverse events [42].                                                                                                                                                                                                                                        |

### **Arm 1: Control:**

Participants randomized to the control arm will not receive any of the Frailty Management Interventions (see Table 1).

### **Arm 2: Group Exercise:**

**Group Exercise:** Participants will attend the exercise program, ***twice-weekly*** (one-hour per class) at a YMCA site for 4-months. In the first 15-minutes, participants will check-in and report any injuries/concerns. The **exercise component** will be an hour of strength/balance exercises and aerobics (walking with activator poles supervised by an instructor) followed by time allotted for participants to **socialize**. The supervised group exercise component will be modeled after existing **LiveWell classes** at the YMCA (e.g., *Balance Plus, In Motion*) but with a greater emphasis on functional movements specifically designed for older adults with frailty and mobility challenges, including modifications for canes/walkers. Principles of balance training from the *Weight-bearing Exercise for Better Balance* [WEBB.org.au; used in the Frailty Intervention Trial [8,15]] will be included. Co-Investigator, [name], a registered physiotherapist and post-doctoral fellow has tailored the existing YMCA programs to meet the needs of older adults living with frailty based on challenging, safe, progressive evidence-based exercises: 1) resistance 2) balance 3) aerobic 4) static and 5) dynamic stretching (flexibility) in addition to a warm-up and cool-down. **Supplemental Home Exercise:** In accordance with recent guidelines to ***achieve 3 hours/week*** for fall prevention practice in older adults [14], participants will be provided with a tailored home-exercise program developed by a physiotherapist to gain an additional 1-hour of physical activity (e.g. 3 sessions of 20 min). Home-based exercises will be re-evaluated on a monthly basis by the study physiotherapist to ensure exercises are at the appropriate level of challenge. **Intervention fidelity (standardizing the delivery):** Instructors will undergo training on topics specific to working with older adults living with frailty.

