### **Arm 3: Multi-modal Intervention:**

**Group Exercise/Supplemental Home Exercise:** This will be delivered identically to Arm 2. **Oral Nutritional Supplementation:** As piloted in our Virtual Frailty Rehab Study, the ONS (each serving) contains 225kcal, and 11-12 grams protein (Glucerna, Ensure). Abbott Nutrition has provided support to this study in relation to the Abbott products Ensure® and Glucerna®. Participants are advised to take this with a meal or within 3 hours of exercise on activity days. Participants will be provided with two ONS each day of the study. The research staff will schedule Arm 3 participants for an initial and post assessment appointment. Working in consultation with the study geriatricians and pharmacist, as required, the multi-modal arm assessment will include: 1) Reviewing the participants' relevant medical and medication history at the baseline assessment (using the medical and medication history form completed and collected by study personnel). **Nutrition review:** Conduct nutritional screening flow (developed by a consultant dietician) and review any questions, provide some additional counseling/coaching at follow-up visits. ONS will be provided to all participants unless contraindicated. **Medication review:** Review/update current medication list (baseline medical history form) and forward the list and medical history to the consultant study pharmacist. Prior to the medication review, we will also be requesting permission from the participant to contact their family physician and community pharmacist to receive their medication list. The Beers and START/STOPP criteria will be considered to provide

PROTOCOL

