**Figure 1: Study Schema**

[figure not shown]

**4.7. Monitoring Compliance:** The study team is well aware of the barriers encountered with compliance when working with vulnerable older adults, which includes transportation challenges, caregiver burden, medical concerns, indifference, cognitive limitations and poor health [45]. Class attendance will be tracked via YMCA attendance monitoring. Participants will be asked to track weekly adherence to home and group exercises, nutrition (ONS, monthly diet food log, and vitamin D), and falls/adverse events in log-books. Study personnel will conduct monthly check-ins by phone to check-in on adverse events and to assess and assist with challenges pertaining to their intervention. In the GERAS DANCE pilot study for cognitively impaired/pre-frail older adults, we have overcome a number of recruitment challenges and we can apply this learning. For example, YMCA trained volunteers will greet and assist participants to ensure safety on arrival. Furthermore, this group of investigators has extensive experience running such trials and can draw on existing infrastructure and past experiences [e.g., Health TAPESTRY [46]; Cardiovascular Health Awareness Program [47]; Vitamin D and Osteoporosis Study (ViDOS) [48,49]].

**4.8. Trial outcomes:** Primary, secondary, and exploratory outcomes will be assessed at **0 and 4-months**. Healthcare utilization will be tracked (via monthly phone-call by research personnel) during the intervention phase and for an **additional 6-months** following the intervention. The primary outcome measures are the Short Performance Physical Battery (SPPB) [50] and 400m Walk Test [51] (**Table 2**). The **SPPB was the primary outcome of the first frailty intervention trial** [8] and demonstrated improvement in both the FIT study and the LIFE trial, the largest physical activity study in older adults, to date [52,53]. SPPB total scores range from 0-12, and  $\leq 7$  is an established cut-off for poor physical performance. A substantial clinical meaningful change in total SPPB score is 1.3 points [54]. A clinically significant change is considered in the range of 0.05 with 0.10 considered a substantial shift in scores [55].

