**FRAILTY REHABILITATION: A COMMUNITY-BASED INTERVENTION TO PROMOTE HEALTHY AGING**

pain with exercise, dizziness, chest pain, death or any other event from any source will be reported to the research team and recorded on a structured form. If applicable under the regulations governing the study, the research staff shall report adverse events that occur during the course of the study to Abbott Nutrition. The research staff shall also report all periodic reports regarding the study to Abbott Nutrition along with any safety issues related to the study or safety signal associated with the Abbott Nutrition study product.

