# PROTOCOL

## **FRAILTY REHABILITATION: A COMMUNITY-BASED INTERVENTION TO PROMOTE HEALTHY AGING**

|                                             |  |                |                |   |
|---------------------------------------------|--|----------------|----------------|---|
| Cognition                      |  | X              | XX             |   |
| QoL  & ADL/IADLs  |  | X              | X              |   |
| Life Space Mobility            |  | X              | XX             |   |
| Depression/ Mood               |  | X              | XX             |   |
| Nutrition                      |  | X              | X              |   |
| Functional Mobility            |  | X              | X              |   |
| Accelerometer Data                          |  | X              | X              |   |
| Muscle Mass                    |  | X † | X † |   |
| Falls and Adverse events (monthly)          |  |                | XX             | X |

Demographics= Age, Gender, Housing, Education, Smoking Status, Falls, Hospitalizations, Walking Aid, Fractures, Past Surgeries, Chronic Conditions, Dietary Supplements, Multivitamins, Calcium supplements, Oral Nutritional Supplements, Physical Activity.

Healthcare Use= number of GP visits/ walking clinic, number of specialist visits, number of physiotherapy visits

Physical Measurements= height and weight, heart rate and blood pressure

Physical Function= Short Physical Performance Battery (SPPB)

Muscle Strength = grip strength with handgrip dynamometer [kg]

Frailty Measures= Frailty Index (as measured by the GERAS Fit-Frailty App)

Mobility= 400m walk test and Modified Rating of Perceived Exertion (RPE) Scale post-400m walk test.

Sarcopenia= SARC-F questionnaire, 5-time chair stand test (via SPPB)

Fear of Falling= Icon Falls Efficacy Scale (ICON-FES)

Barriers to exercise and transportation= interest in having a healthy level of activity and eating well, exercise barriers, side effects to exercise, facilitators to exercise, barriers to transportation to the YMCA

Cognition= Montreal Cognitive Assessment (MoCA)

QoL (Quality of Life)= EQ-5D-5L Questionnaire

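### Class check-ins give Arms 2 and 3 an injury-reporting route that control lacks and the protocol asks for no source of report, so an all-source comparison of minor harms by arm risks over-counting in the exercise arms

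*Protocol*

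**What the plan says.** Protocol section 4.6 describes the Arm 2 programme as follows: "Participants will attend the exercise program, *twice-weekly* (one-hour per class) at a YMCA site for 4-months". Each participant is prompted at class: "In the first 15-minutes, participants will check-in and report any injuries/concerns". For Arm 3, the exercise component is the same: "This will be delivered identically to Arm 2". Control receives none of the listed interventions, so it has no classes.

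Three other reporting routes carry no arm restriction. Section 4.7 has falls and adverse events entered in log-books, and adds a call: "Study personnel will conduct monthly check-ins by phone to check-in on adverse events". Appendix B schedules the same collection as "Falls and Adverse events (monthly". Section 9.0 tells participants to contact the coordinator themselves about any unwelcome symptom.

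On recording, section 9.0 lists falls, fracture, pain, dizziness and similar events, and ends the list: "or any other event from any source will be reported to the research team and recorded on a structured form". It does not mention the route of report.

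On balance of contact, section 4.6 says: "All participants will receive equal amounts of contact and follow-up by research personnel (e.g., monthly phone-calls, outcome assessments". Yet for the multi-modal arm it also says: "The research staff will schedule Arm 3 participants for an initial and post assessment appointment". Arm 3 further has coaching at follow-up visits and a research-staff check on whether medication recommendations were taken up.

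**The concern.** Section 8.0 names falls, musculoskeletal injury and fatigue as the risks of the exercise classes and assessments, and section 9.0 adds pain and dizziness. Whether minor events of this kind are recorded depends heavily on whether someone asks. Two arms are asked at class and the third is not, and participants and instructors know the allocation (section 4.5). Equal true rates could then look like extra harm from exercise, or a real reduction in falls could be masked.

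The by-arm picture matters because section 7.0 lets the monitoring board recommend changes or termination, and section 6.0 commits to reporting under CONSORT. The problem lies in data collection. If the route is not noted when the event is recorded, no later analysis can reliably separate class-detected events from those found by routes open to every arm.

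**Working it through.** The protocol states no figure on this point, so there is none to reproduce. The check compares the routes by arm, counts prompts, and then asks what the imbalance could do to a ratio.

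**1. Routes by arm**

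| Route | Protocol section | Arm 1 | Arms 2 and 3 |
|---|---|---|---|
| Class check-in on injuries or concerns | 4.6 | No | Yes |
| Log-book | 4.7 | Yes | Yes |
| Monthly call | 4.7, Appendix B | Yes | Yes |
| Self-report to coordinator | 9.0 | Yes | Yes |
| Extra research-staff contacts | 4.6 | No | Arm 3 only; not described as event collection |

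The class imbalance applies to the four months of classes only.

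**2. Prompts over four months**

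- Weeks: 4 × 365.25 / 12 / 7 = 17.4.
- Classes: 2 × 17.4 = 34.8, about 35. At an assumed 80% attendance, 0.8 × 34.8 = 27.8, about 28.
- Scheduled common occasions: 4 calls plus about 17.4 log-book entries = 21.4. This takes the log-book as weekly, which is how section 4.7 reads but which it does not state separately for adverse events.
- Arms 2 and 3: 21.4 + 34.8 = 56.2, a ratio of 56.2 / 21.4 = 2.6. At 80% attendance: (21.4 + 27.8) / 21.4 = 2.3.

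Self-report is unscheduled and is not counted. That the check-in happens at every class is a fair inference from the text, not an explicit statement.

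**3. From prompts to counts**

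More prompts do not mean proportionately more events. Let p be the probability that the common routes catch an event (taken as equal in all arms), and r the share of the events they miss that the class check-in catches. With equal true risk, the apparent ratio of Arms 2 and 3 to control is [p + (1 − p)r] / p. The documents give neither p nor r, so every value below is an assumption.

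| p | r | Captured, exercise arms | Ratio |
|---|---|---|---|
| any | 0 | p | 1.00 |
| 0.90 | 0.50 | 0.95 | 0.95 / 0.90 = 1.06 |
| 0.80 | 0.50 | 0.90 | 0.90 / 0.80 = 1.13 |
| 0.70 | 0.67 | 0.90 | 0.90 / 0.70 = 1.29 |
| 0.60 | 0.75 | 0.90 | 0.90 / 0.60 = 1.50 |

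The ratio is never below 1, and exceeds 1 as soon as the class check-in catches anything the common routes miss. As p approaches 1, as is plausible for deaths, fractures and hospitalizations, the ratio approaches 1 whatever r is.

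**4. What restriction to common routes could do**

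The formula holds p equal across arms. A participant who has told the instructor about a fall may not mention it again on the call. If common-route capture then fell to, say, 0.70 in the exercise arms against 0.80 in control, the restricted ratio would be 0.70 / 0.80 = 0.88, a bias in the other direction. A restriction is therefore sound only if the call asks about all events, including those already reported.

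**The case against.** The strongest reply is that the protocol specifies no harms comparison at all. Falls and adverse events are not among the outcomes in Table 2, section 6.0 and Table 3 contain no harms analysis, and the choice of sources for a comparative table can be left to an analysis plan. This stands as far as it goes. A reader might infer that a planned comparison is biased, and the documents support only that an all-source comparison would be at risk. It does not dispose of the point, because an analysis plan cannot use a source that was never recorded.

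Four other strong inferences should also be resisted.

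- That control is followed only by log-book and call. Section 9.0 gives every arm self-report to the coordinator.
- That the exercise arms have about 35 occasions against 4. This leaves out the log-book; with weekly entries the ratio is about 2.6.
- That the over-count could reach 1.9. This needs p = 0.50, r = 0.90 and class capture independent of the other routes (0.95 / 0.50 = 1.90). Nothing in the documents supports those values, and full overlap of the routes gives 1.00.
- That the classes contradict the equal-contact sentence. It speaks of research personnel, and section 4.5 classes instructors as intervention personnel. The Arm 3 appointments and medication follow-up do strain it. The monthly physiotherapist review of home exercise in Arms 2 and 3 is not said to be in person.

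The phrase in section 9.0 about events from any source may mean any cause, not any channel. Either way, events go to the research team and onto one form with no route mentioned. The class prompt also covers injuries and concerns, not every kind of adverse event.

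**Conclusion.** The point holds in a limited form. Ascertainment is unequal by design: Arms 2 and 3 have a class prompt that control cannot have, on top of three routes without arm restriction, and the protocol does not ask for the source of each event. An all-source comparison of falls and minor adverse events by arm is therefore at risk of over-counting in Arms 2 and 3. The direction rests on two assumptions: that class check-ins catch some events the common routes miss, and that such reports reach the event form. The size cannot be derived from the documents; the range of 1.00 to 1.50 is illustration only. Serious events are little affected and the primary outcomes are untouched. The change should be made because it costs almost nothing and the missing information cannot be recovered afterwards.

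**What to change.** - Add a field to the event form for the source of the report: class, call, log-book, self-report or study visit. Allow more than one.
- Have the monthly call ask every participant, in all arms, about all falls and adverse events since the last call, whether or not already reported at class.
- State in section 9.0 that any between-arm comparison of falls and non-serious events rests on the routes common to all arms. An event reported by both kinds of route keeps its common-route flag. Show all-source counts alongside, and list class-only or visit-only events separately for safety oversight.
- Reword the equal-contact sentence in section 4.6 so that it claims equality for the monthly calls and outcome assessments only.

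The cost is one form field, a line in the call script and a few sentences of protocol text. The comparative table will hold slightly fewer events. The class check-in stays as it is, and all events are still collected and reviewed.
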